### Study population and recruitment

Participants will be recruited at the Department for Oncology and Hematology of the Clinic Northwest and at the Department for Gynecology at the University Clinic in Frankfurt (Germany). Patients with initial diagnosis of mammary carcinoma stage I-IIIA and scheduled chemotherapy, not fulfilling any of the listed exclusion criteria in Table 2, will be recommended for study participation by the attending physician to the principal investigator. Patients will receive detailed descriptions of the study and will be given sufficient time to ask any questions. Patients will be included in the planned study only after they will give written informed consent. The participants will be included chronologically.

**Table 2 Tab2:** Objectives and hypotheses of the study

Objectives	Hypotheses
Main objective • To evaluate the effects of a HIIT versus placebo, conducted simultaneously with first-line chemotherapy regimen on CRCI, in women with breast cancer	Main hypothesis • In women with breast cancer, the decline in HVLT-R-, TMT-A/B- and COWAT test performance from baseline to completion of the exercise-intervention, is significantly smaller in the HIIT group compared to the control group (hypothesis A)
Secondary objective • To evaluate the effects of a HIIT versus placebo, conducted simultaneously with first-line chemotherapy regimen on self-perceived cognitive performance, in women with breast cancer	Secondary hypotheses • In women with breast cancer, the decline of FACT-COG scores from baseline to completion of the exercise-intervention/to 6-months follow-up^a^_,_ is significantly smaller in the HIIT group compared to the control group (hypothesis B)
• To evaluate the effects of a HIIT versus placebo, conducted simultaneously with first-line chemotherapy regimen on executive functioning subdomain response inhibition, in women with breast cancer	• In women with breast cancer, the decline of INHIB performance from baseline to completion of the exercise-intervention/to 6-months follow up, is significantly smaller in the HIIT group compared to the control group (hypothesis C)

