• To evaluate the effects of a HIIT versus placebo, conducted simultaneously with first-line chemotherapy regimen on anxiety, fatigue, quality of life, sleep disturbances and chemotherapy compliance, in women with breast cancer	• In women with breast cancer, the change of HADS-D, MFI-20, EORTC-QLQ-C30, QOL-BR23 and PSQI scores from baseline to completion of the exercise-intervention/to 6-months follow up, is significantly more favorable in the HIIT group compared to the control group (hypothesis I)
• To evaluate the sustainability of the effects of a HIIT versus placebo conducted simultaneously with first-line chemotherapy regimen on CRCI in women with breast cancer	• In women with breast cancer, the decline in HVLT-R-, TMT-A/B- and COWAT test performance from baseline to 6-months follow up is significantly smaller in the HIIT group compared to the control group (hypothesis J)
Exploratory mediation analysis	
• To evaluate if the change in proinflammatory marker expression, from baseline to completion of the exercise-intervention, partially mediates the effect of the exercise intervention on the change of cognitive performance, from baseline to completion of the exercise-intervention, in women with breast cancer.	• In women with breast cancer, there is a significant indirect effect of exercise intervention on the change of HVLT-R−/TMT-A/B-/COWAT test performance, from baseline to completion of the exercise-intervention, through the change of TNF-α/IL-6/IL-1α/IL-1β/CRP serum level, from baseline to completion of the exercise-intervention (hypothesis K)
• To evaluate if the change in antiinflammatory marker expression, from baseline to completion of the exercise-intervention, partially mediates the effect of the exercise intervention on the change of cognitive performance, from baseline to completion of the exercise-intervention, in women with breast cancer.	• In women with breast cancer, there is a significant indirect effect of exercise intervention on the change of HVLT-R−/TMT-A/B-/COWAT test performance, from baseline to completion of the exercise-intervention, through the change of IL-1RA/IL-10 serum level, from baseline to completion of the exercise-intervention (hypothesis L)

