### Primary endpoint

The primary endpoint of the present study will be the change of test-scores from baseline (t_0_) to after completion of the exercise intervention (t_1_), in the test battery recommended by the International Cancer and Cognition Task Force (ICCTF) to capture CRCI [59]. The ICCTF test battery comprises of the Hopkins Verbal Learning Test – Revised (HVLT-R), Trail-Making-Test A/B (TMT-A/TMT-B) and the Controlled Oral Word Association Test (COWAT).The HVLT-RThe HVLT-R was developed to measure forgetfulness in the domain of verbal memory in individuals at the age of 16 and older [67]. The test includes a list of 12 nouns, which will be read to the participants. Then, the participants will be instructed to repeat as many words from that list as they can remember in any order. This process will be repeated three times. The sum of correct recalled words at all 3 learning trials (“Total-Recall”) has been described as measure of learning efficiency and short-term verbal memory [68] and will be used for analyses. The HVLT-R offers six parallel forms. As recommended for repeated testing, the parallel forms 1, 2 and 4 will be used at t_0_, t_1_ and t_2_ [68]. The order of test forms at the 3 measurement time points will be random but counterbalanced across participants. The HVLT-R shows adequate psychometric properties [69, 70].TMT-A/BThe TMT-A will instruct participants to connect randomly distributed numbers from 1 to 25 as quickly and as correctly as possible, in ascending order. The time participants require for completing TMT part A has been described as a valid measure of selective attention [71] and will be used for analyses in the planned study. TMT-B will instruct participants to connect randomly distributed numbers (1 to 13) and letters (A to L) in ascending order, alternating between numbers and letters as quickly and as correctly as possible. The time participants require for completing TMT part B has been reported as valid measure of executive functioning subdomain set-shifting [71] and will be used for analyses. In the present study, the Langensteinbacher version of the TMT (TMT-L) [72] will be applied. It will be operated via the Wiener Test-System (WTS) (Schuhfried, Vienna, Austria) and adequate psychometric properties have been reported for it [72]. TMT-L parallel versions S1, S2 and S3 will be used in a random order at the 3 measurement time-points, but counterbalanced across participants.COWATThe German version of the COWAT will be used in the present study [73]. Participants will be instructed to name as many words as possible in one min, beginning with a given letter. As recommended in the German test-manual [73], the letters S, P and M will be used at the 3 measurement time points. The order of the letters will be random, but counterbalanced across participants. The number of words participants will produce will be used for analyzation. Adequate psychometric properties for the German version of the COWAT have been reported [73].

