### Statistical analysis

An intention to treat (ITT) analysis will be performed We will also assess the effect of the complete treatment in a per protocol analysis. Separate 2 × 3 mixed ANCOVAs will be conducted to determine the effects of between-subjects factor exercise-intervention, within-subjects factor measurement time-point and their interaction on primary and secondary outcomes. Patients’ baseline scores of each specific parameter will be used as covariate. A significant main effect, of within-subjects factor measurement time-point, will be further investigated through Bonferroni corrected post hoc pairwise comparisons. Simple effects analyses will be conducted to determine potential group differences at each measurement time-point.

ANCOVA assumptions will be explored. In case of violations of normality assumption, appropriate nonparametric procedures will be used. In case of violations of ANCOVA assumptions of homogenous variances or sphericity, F-test will be adjusted. Eta-square values will be reported as effect size estimates for explained variance, and Cohen’s d values will be reported for post hoc pairwise comparisons.

In addition, an exploratory regression-based mediation analysis will be performed for each intervention induced change in biomarker expression. It will be tested if the change in biomarker expression, from baseline to completion of the exercise intervention, partially mediates the effect of the exercise intervention on the change in cognitive performance. The indirect effect, as combined effect of intervention induced change in biomarker and change in biomarker induced change in cognitive performance (i.e. the effect of mediation), will be calculated (product of regression coefficients). The 95% confidence intervals will be created around the indirect effect using bootstrapping [90, 91].

Statistical analysis will be performed by a statistician blinded to treatment groups. Statistical analyses will be conducted using SPSS 25® (IBM®, Armonk, NY, USA). For mediation analyses, the PROCESS custom dialog box (version 3.1, Model 4) for SPSS [91] will be used. A result will be considered significant at *p*-value equal to or less than .5 (in case of primary endpoint this will be adjusted to .0125).

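### The 2 × 3 mixed ANCOVA uses the baseline score as both a repeated outcome and the covariate, and no planned comparison is designated as the primary test at .0125

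*Protocol article*

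**What the plan says.** All statements are in the protocol article.

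- **Model (Statistical analysis).** "Separate 2 × 3 mixed ANCOVAs will be conducted to determine the effects of between-subjects factor exercise-intervention, within-subjects factor measurement time-point and their interaction". The same model serves primary and secondary outcomes. The next sentence adds that patients' "baseline scores of each specific parameter will be used as covariate".
- **Time-points (Data collection and timeline; Primary endpoint).** Outcomes are measured at t0, t1 and t2 and at no other time. The parallel versions of the Trail-Making-Test, for example, are "used in a random order at the 3 measurement time-points".
- **Follow-up tests (Statistical analysis).** A significant time main effect leads to Bonferroni-corrected pairwise comparisons. Separately: "Simple effects analyses will be conducted to determine potential group differences at each measurement time-point".
- **Primary endpoint.** "The primary endpoint of the present study will be the change of test-scores from baseline" to the end of the intervention (t1). Hypothesis A in Table 2 covers the same interval. The 6-month result on the same tests is secondary hypothesis J.
- **Sample size calculation.** An ANCOVA of one post-treatment score with baseline as covariate, d = .5, alpha .05/4 = .0125, power 80%, ρ = .6, giving 59 per group.
- **Threshold (Statistical analysis).** The .0125 level is tied to the primary endpoint, not to a particular model term.

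**The concern.** With three measurement occasions, a three-level time factor has to include baseline. Putting the same baseline score on the right-hand side makes one of the three outcome levels a copy of the covariate. The omnibus tests that the section names first then answer a question about t1 and t2 together, while the primary endpoint concerns t1 alone.

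The result that counts as primary is at stake. If the interaction or the group main effect were read as the test of hypothesis A, its power would depend on what happens six months after the intervention, and a purely late effect could make it significant. The 80% power in the sample size section belongs to neither test.

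**Working it through.** **1. The plan's own figure.** A two-sample t-test with d = .5, two-sided alpha .0125 and power .80 needs 91 per group (noncentral t). The article's factor is 1 − ρ² = 1 − .36 = .64. Then 91 × .64 = 58.24, rounded up to 59 per group, 118 in total. The stated figure is reproduced. Power of the t1 ANCOVA at 59 per group: standard error √(2 × .64/59) = .147, noncentrality .5/.147 = 3.39, 115 degrees of freedom, power 80.3%.

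**2. What the double use of baseline does.** Let δ1 and δ2 be the baseline-adjusted group differences at t1 and t2.

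- At t0 the outcome equals the covariate, so the fitted value is exact. The residual sum of squares is zero (about 10⁻²⁹ numerically) and the adjusted group difference is zero. Its test statistic is 0/0, so the simple effect at t0 cannot be tested.
- The group main effect tests (0 + δ1 + δ2)/3 = 0, which is the same test as (δ1 + δ2)/2 = 0.
- The interaction tests whether 0, δ1 and δ2 are equal, that is δ1 = δ2 = 0 jointly.
- The simple effect at t1 tests δ1 = 0 with baseline as covariate. That is the ANCOVA of step 1.

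**3. Power of each test.** From the article: 59 per group, alpha .0125, d = .5 at t1, baseline–t1 correlation .6. Assumed, because the article does not give them: baseline–t2 correlation .6, t1–t2 correlation .6 or .8, and the size of the t2 effect. Simulated with 8,000 trials per scenario; the interaction is Greenhouse–Geisser adjusted. Each cell gives the percentage significant at t1–t2 correlation .6 / .8.

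| Effect at t1, t2 | Group main effect | Interaction | Baseline-adjusted t1 contrast |
|---|---|---|---|
| .5, .5 | 94 / 87 | 84 / 86 | 80 / 79 |
| .5, .25 | 70 / 60 | 66 / 75 | 80 / 80 |
| .5, 0 | 31 / 25 | 80 / 91 | 80 / 80 |
| 0, .5 | 32 / 25 | 80 / 91 | 1.2 / 1.4 |
| 0, 0 | 1.1 / 1.4 | 1.2 / 1.4 | 1.0 / 1.4 |

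**4. Closed-form check of the group column.** The residual variance at t1 and at t2 is .64, and the residual covariance is the t1–t2 correlation minus .36. At correlation .6 the covariance is .24, and the variance of the t1/t2 average is (.64 + .64 + 2 × .24)/4 = .44. The standard error is √(2 × .44/59) = .122. For effects (.5, .25) the average effect is .375, the noncentrality is .375/.122 = 3.07, and the power is 70%. For (.5, 0) the average is .25, the noncentrality is 2.05, and the power is 32%. Both agree with the simulation.

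**5. Reading the table.** Only the t1 contrast keeps the planned 80% whatever happens at t2. In the fourth row hypothesis A is false, yet the interaction is significant in 80–91% of trials. In the last row each test, taken alone, stays close to its nominal 1.25%.

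**The case against.** The strongest reply is that the plan already contains the right test. Simple effects at each time-point are planned unconditionally, and with baseline as covariate the one at t1 is exactly the powered ANCOVA. This stands. A reader might infer that the plan does not test its primary endpoint at all. That goes too far: the redundant t0 level does not bias the t1 contrast, which is planned but not singled out.

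The reply continues that the article is consistent about its target (t1 primary, t2 secondary, .0125 for the primary endpoint) and that naming the deciding model term can be left to an analysis plan. The first part stands. The second helps only in part, because the 2 × 3 model with baseline as covariate is stated text and not an omission.

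Two further inferences are tempting and not supported:

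- **Inflated family-wise error.** Under the global null it would be about 12% at a t1–t2 correlation of .6, or about 10% at .8, if the group effect, the interaction, or the simple effect at t1 or t2 could each carry the claim. The article nowhere says that they may, and it makes t2 secondary. The error would exceed 5% only if several of the listed tests were allowed to count. If a significant interaction also had to be confirmed at t1, the error stays below 5% (1.5–3.4%).
- **A time effect as gateway to group comparisons.** The time-effect trigger governs only pairwise comparisons between occasions. The group simple effects are not conditional on it.

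**Conclusion.** The point holds as a misspecified model combined with an undesignated primary test. The double use of baseline follows directly from the text and needs no assumption. It leaves the t0 simple effect untestable and turns the group and interaction terms into tests that match neither the primary endpoint nor the sample size calculation.

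The size of the mismatch rests on the assumed t2 effect, the baseline–t2 correlation of .6 and the t1–t2 correlation of .6 to .8. Over that range, with d = .5 at t1, interaction power is about 66–91% and group-effect power about 25–94%, against about 80% for the t1 contrast. Harm to the primary conclusion arises only if an omnibus term is taken as the primary test, which the article neither states nor excludes. The 59 per group is correct for the t1 contrast.

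**What to change.** In the statistical analysis section, or in the analysis plan before unblinding:

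1. Remove t0 from the within-subject factor. Outcomes are t1 and t2, baseline is the covariate, and the design becomes 2 × 2. Use the same model for the secondary outcomes.
2. State that, for each of the four cognitive scores, the baseline-adjusted HIIT-minus-control difference at t1 is the sole primary test, judged at .0125.
3. Keep the t2 difference secondary, as hypothesis J already has it, and label the group main effect, the interaction and the time comparisons as supportive.

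The cost is a wording change. No new data are needed, and 59 per group stays, with 80.3% power for the named test.

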**Methods:**

A single-blinded randomized controlled trial will be carried out. The impact of HIIT on CRCI will be compared to that of a placebo-intervention (supervised myofascial release training). Both interventions will be conducted simultaneously with the patients’ first-line chemotherapy treatment typically lasting 12–18 weeks. Fifty-nine women with breast cancer will be included in each of the two groups. The study is powered to detect (α = .05, β = .2) a medium effect size difference between the two groups (d = .5) in terms of patients’ change in cognitive testing performances, from baseline until the end of the exercise-intervention. The cognitive test battery, recommended by the International Cancer and Cognition Task Force to assess CRCI, will be used as primary measure. This includes the Hopkins Verbal Learning Test (learning/verbal memory), the Controlled Oral Word Association Test (verbal fluency) and the Trail-Making-Test A/B (attention/set-switching). The following endpoints will be assessed as secondary measures: Go-/No-Go test performance (response inhibition), self-perceived cognitive functioning, serum levels of pro- and antiinflammatory markers (tumor necrosis factor alpha, Interleukin-6, Interleukin-1 alpha, Interleukin-1 beta, C-reactive protein, Interleukin-1 receptor antagonist and Interleukin-10), serum levels of neurotrophic and growth factors (brain-derived neurotrophic factor, insulin-like growth factor 1 and vascular endothelial growth factor), as well as common cancer-related side effects (decrease in physical capacity, fatigue, anxiety and depression, sleep disturbances, quality of life and chemotherapy compliance).

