### Sample size calculation

Sample size calculation was done to investigate the effect of exercise-intervention on the primary endpoint (objectively assessed cognitive performance using test battery of the ICCTF), in an analysis of covariance model (ANCOVA) using G*Power 3.1.9.2 software [87]. It was hypothesized that the changes in the test scores in the ICCTF test-battery, from baseline to after completion of the exercise-intervention, differ significantly between the HIIT group and the PCG-training group. Previous studies have shown that regular, low to moderate, exercise exerts rather small beneficial effects on CRCI in breast cancer patients [44–48]. However, pronounced effects of HIIT on fitness, cardiovascular health, fatigue and biomarkers have been reported in cancer patients [55–58]. Changes in these factors are discussed to play a pivotal role in the genesis of CRCI [24]. In accordance with it, we expect more meaningful effects of HIIT on CRCI compared to low to moderate exercise interventions. A medium effect of d = .5 was defined for sample size calculation. Alpha was set at 5%, but Bonferroni corrected due to multiple testing (4 outcome variables), leading to an adjusted alpha of 1.25%. Test power (1-β) was set at 80%. Participants’ test scores at baseline are included as covariate in the model. Required sample size in such an ANCOVA model can be calculated as (1-ρ^2^)*n, with ρ representing the correlation between participants’ baseline and post-treatment outcome-scores and n representing the sample size that would have been required, if a t-test of post-treatment outcome-scores was applied [88]. The correlation between patients’ test scores at baseline and at t_1_ was estimated with ρ = .6. This estimation was based on preliminary results (*N* = 40) of an ongoing trial of our group [89], indicating correlations between baseline and post-intervention measures of the applied tests of .6 and .8. Under the presuppositions made, the sample size calculation showed that 59 patients would be required in each group (*N* = 118). Based on attrition rate reported in existing studies applying HIIT in breast cancer patients during chemotherapy [49, 51] we accounted for 15% drop-out rate, leading to a total sample size of *N* = 136 patients.

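### The general significance threshold is printed as p ≤ .5 where the plan's own figures require .05, and it is the only rule given for secondary hypotheses B to J

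*Protocol article*

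**What the plan says.** The last sentence of the Statistical analysis section (protocol article, Methods) gives the decision rule. A result counts as significant at a p-value "equal to or less than .5 (in case of primary endpoint this will be adjusted to .0125"). The bracket covers the primary endpoint; everything else falls under the .5.

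Three other places give the level differently:

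- Abstract, Methods: "The study is powered to detect (α = .05, β = .2) a medium effect size difference between the two groups (d = .5").
- Sample size calculation: "Alpha was set at 5%, but Bonferroni corrected due to multiple testing (4 outcome variables), leading to an adjusted alpha of 1.25" per cent.
- Statistical analysis, mediation paragraph: the indirect effects get 95% bootstrap confidence intervals, which correspond to a 5% level.

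The article gives no other threshold for the secondary endpoints. In Table 2 (objectives and hypotheses), each of hypotheses B to J predicts a significantly smaller deterioration, or a significantly more favourable change, with HIIT than with control.

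**The concern.** The printed threshold is ten times the alpha used elsewhere in the same article. Under a true null hypothesis, a valid continuous p-value is at or below .5 half the time, so a test at that level does not separate an effect from noise.

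The secondary hypotheses cover self-perceived cognition, response inhibition, ten serum markers, physical fitness, five questionnaires and the six-month persistence of any cognitive effect. Whether each is supported depends on this one sentence. The article is also the public record of what was specified in advance, so a reader who later checks the reported secondary results against it will find a rule that nearly any result could meet.

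**Working it through.** **1. Which base level gives .0125?** The Sample size calculation section names a Bonferroni correction over four outcome variables.

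- .05 / 4 = .0125, which matches both the 1.25% in that section and the .0125 in the decision rule.
- .5 / 4 = .125, which matches neither.

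**2. Does the sample size confirm it?** The inputs, all from the Sample size calculation section, are:

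- effect size: "A medium effect of d = .5 was defined for sample size calculation"
- power: "Test power (1-β) was set at 80" per cent
- correlation: "The correlation between patients’ test scores at baseline and at t_1_ was estimated with ρ = .6"
- adjusted alpha .0125
- the article's formula, n × (1 − ρ²), where n is the t-test sample size and 1 − .6² = .64.

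The article does not say whether the test is one- or two-sided, so both were tried with the exact (noncentral t) calculation.

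| Alpha used | Sides | t-test n per group | × .64 | Rounded up |
|---|---|---|---|---|
| .0125 | 2 | 91 | 58.24 | **59** |
| .0125 | 1 | 78 | 49.92 | 50 |
| .05 (no correction) | 2 | 64 | 40.96 | 41 |
| .125 (= .5/4) | 2 | 46 | 29.44 | 30 |

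The plan's figure ("the sample size calculation showed that 59 patients would be required in each group") comes back only at two-sided .0125. An ANCOVA F-test with f = .25/√.64 at the same alpha needs N = 118, again 59 per group. The base level behind the design is therefore 5%, tested two-sided.

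**3. How many tests does the .5 govern?** Outcomes named in Table 2:

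| Hypothesis | Outcomes | Count |
|---|---|---|
| B | FACT-COG | 1 |
| C | INHIB | 1 |
| D | TNF-α, IL-6, IL-1α, IL-1β, CRP | 5 |
| E | IL-1RA, IL-10 | 2 |
| F | BDNF | 1 |
| G | VEGF, IGF-1 | 2 |
| H | W/kg, VO2peak | 2 |
| I | HADS-D, MFI-20, EORTC-QLQ-C30, QOL-BR23, PSQI | 5 |

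That is 19 outcomes. Each is stated for two contrasts (baseline to end of intervention, baseline to six-month follow-up), so 19 × 2 = 38. Hypothesis J adds HVLT-R, TMT-A, TMT-B and COWAT at follow-up, giving 38 + 4 = 42, before any questionnaire subscales.

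**4. Expected false positives if every null were true** (number of tests × alpha; this does not require independence):

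| Count used | At .5 | At .05 |
|---|---|---|
| 42 tests, either direction | 21 | 2.1 |
| 42 tests, favouring HIIT only (half of a two-sided alpha) | 10.5 | 1.05 |
| 19 tests (one group comparison per outcome, B to I) | 9.5 | 0.95 |

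The ratio is ten in every row.

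**The case against.** The strongest reply is that this is a misprint that nobody would apply. The same sentence contains .0125, which can only come from .05, and the abstract, the sample size section and the 95% intervals all agree. A careful reader can recover the intended rule, and the primary inference is untouched. That is a fair account of how the error arose. It does not remove the error, because the sentence is the sole written criterion for the secondary hypotheses and the alpha in the sample size section is set for the primary endpoint.

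Two points on scope also stand:

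- The rule does not reach every non-primary result. The mediation hypotheses K to N have 95% bootstrap intervals. The Bonferroni-corrected pairwise comparisons of time points are not a real exception, since .5 divided by three pairs is still about .167.
- The figure of 42 is a count derived from Table 2. The section itself plans one 2 × 3 mixed ANCOVA per outcome. The figure of 21 counts significance in either direction under a global null, while the hypotheses are directional, so about 10 is the better number for false claims of benefit.

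Neither point changes the contradiction or its correction.

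**Conclusion.** The concern holds. The general threshold of .5 contradicts the article's own 5% alpha by a factor of ten and cannot be the level from which .0125 was derived. Applied literally to hypotheses B to J, it would pass half of all true-null comparisons in one direction or the other, and a quarter in the direction favouring HIIT.

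The expected counts assume that all the null hypotheses are true and that Table 2 is read as 42 separate contrasts; the tenfold ratio depends on neither. The favourable-direction figure also assumes symmetric two-sided tests, which the article does not state. That is inferred from the non-directional wording of the sample size hypothesis (test-score changes "differ significantly between the HIIT group and the PCG-training group") and from the reproduced 59 per group.

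The threshold must be corrected because it is a decision rule on which the trial's secondary conclusions depend. The .0125 threshold, the 80% power and the 59 per group stand.

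**What to change.** In the last sentence of the Statistical analysis section, replace .5 with .05 and state that tests are two-sided. Keep .0125 for each of the four primary tests, which holds their family-wise level at 5%. The analysis plan was not available for this review; if it repeats the sentence, make the same correction there. Since the article is the public record, a short correction notice is the natural place for the change.

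The cost is one character plus the word for sidedness. No new data, redesign or recalculation of the sample size is needed. The change should be dated before the secondary results are analysed, so that it cannot be read as a choice made after seeing them.
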